#### Treatment group: VR-based intervention

Patients allocated to the VR-based intervention followed the standard protocol after surgery as prescribed by the current medical personnel and exposed for 15 min to an interactive virtual environment (i.e., Nature Treks© VR). This application is a commercially available app from the Oculus store (available at https://www.oculus.com/experiences/go/1723271804396968/), promoting relaxation through fifteen highly immersive environments. Each environment recreates a different natural scene (e.g., a tropical beach, savannas at sunset, snowy forests) which can be explored by the patients through a controller. Concomitant with the activities (e.g., walking on the beach, climbing the mountains) environmental effects are changing smoothly to create a vivid experience. Additionally, in some environments (i.e., deep blue and black beginning), patients can freely explore the scenes in 360 degrees for enhancing the feeling of presence and immersion.

As previous studies testing the efficacy of the analgesic effect of VR [30] showed that better immersion is associated with lower scores for pain intensity, the device used is an Oculus Rift® (available at - https://www.oculus.com/). This device is the premium device from Oculus, equipped with a highly immersive headset, one controller, and integrated headphones.

Five minutes before and during the VR exposures, the fluctuations of skin conductance (SC) were measured for all patients. Before and after the intervention, pain intensity, relaxation, and VR adverse effects were assessed. Additionally, the catastrophizing level, anxiety, and depression related to health and presence in the VR environment were quantified.

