### Data collection procedure

Figure 2 offers an overview of the process of the data collection and measures. There is no anticipated harm and compensation for trial participation. This trial does not involve collecting biological specimens for storage. All psychological and physiological measures were collected by a previously trained researcher which had weekly meetings with RG and HS to discuss the potential difficulties and assess the adherence to the study protocol. The level of pain intensity and relaxation was collected before and after the exposure to VR environments in the experimental group, respectively before and after physiological measures in the control group. The SC was measured during the exposure to VR content in the experimental group and for a period of 15 min in the control group. For ensuring an accurate baseline for the physiological measure and for controlling the individual differences in SC, the signal of SC for each participant was taken before the study procedure start for 5 min. During this time, participants had no other instructions, and the communication was maintained at the minimum level. The amount of analgesic consumption for each participant will be extracted from the medical records. Excepting for the fluctuations of skin conductance, all measures were collected through an online platform.

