## Measures

### Primary measures

#### Pain

The pain intensity was measured using the Numerical Rating Scale (NRS) [41] by asking participants to report their intensity before and after the intervention on a scale from 0 (“no pain”) to 10 (“extremely painful”). To help patients to discriminate between different pain levels, they were asked to report the mean level of pain intensity in the last 24 h, the peak of intensity in the same period, and the intensity right before the intervention. We chose NRS for this study rather than other measures more extensively used, such as visual analog scales (VAS), due to the consensus of the better psychometrics properties [42–45]. The value of pain right before the intervention will be used in the analysis of VR effectiveness.

Concomitantly, as a physiological indicator of postoperative pain were measured the fluctuations of the SC [46–48]. The SC were measured using the BIOPAC MP150 system (Biopac Systems, CA,USA). The two finger electrodes were attached to the first phalange of the index and medius fingers from the non-dominant hand with Velcro straps. The electrodes were connected to the computer using the USB connection input. To ensure good contact with the skin, isotonic gel was added to the electrodes prior to attaching to the fingers. At the beginning, participants had few minutes to relax, get ready and comfortable with the experimental environment. After that, patients were instructed not to move for the duration of the recording.

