### Statistical analysis

#### Preliminary analyses and preprocessing data of skin conductance

Demographic characteristics and psychological measures will be explored for missing data, and distribution abnormalities. Means and standard deviations will be used to characterize the sample. Preprocessing of skin conductance measure will be performed using AcqKnowledge 4.1 first through the visual inspection of the raw signal, and then applying the smoothing function with a smoothing factor of three samples. This function has the same effect as the low pass filter by replacing the high-frequency signal with the mean values across three milliseconds to subtract the artifacts, without changing the wave form.

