#### Main analyses

Behavioral data will be analyzed using STATA 16.1 in accordance with the intent to treat principal [56]. Descriptive statistics (i.e., age, gender, assessment of mood, pain catastrophizing, opioid consumption, level of pain intensity, level of relaxation) for the baseline values will be presented within each randomized group. These will include counts and percentages for binary variables and mean and standard deviations, or medians with lower and upper quartiles, for continuous variables, along with minimum and maximum values and missing values. There will be no tests of statistical significance or confidence intervals for differences between randomized groups on any baseline variable. The effectiveness of the intervention on pain intensity (primary outcome) will be assessed by employing random coefficient analysis. We will include the time of assessment, group assignment (VR intervention and standard of care), and the interaction between time of assessment and group in the multi-level regression model. Similarly, for the secondary outcome’s measures (relaxation, time spent by patients thinking about pain, and treatment satisfaction and presence) random coefficient analysis will be performed. Although the intervention is minimally invasive, the adverse effects of the VR intervention will be measured with SSQ scale and pre-post differences will be assessed by *t*-test statistic or the non-parametric equivalent. Physiological data will be processed using the AcqKnowledge 4.1 software, and for each patient, a difference score in the area under the curve between the last 5 min of measurement and baseline level of SC will be extracted. Pearson correlation will be employed to examine the relationship between the level of SC and pain intensity (as a difference score between pre-post intervention). A *P* value will be used to estimate statistical significance for all analyses.

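### The skin-conductance score (area under the curve) does not measure the named pain indicator (fluctuations), and the three-sample smoother removes only high-frequency noise

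*Protocol article*

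**What the plan says.** All references are to the protocol article.

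- **Named indicator.** Under Primary measures, Pain: "as a physiological indicator of postoperative pain were measured the fluctuations of the SC". The section on the VR-based intervention agrees: "Five minutes before and during the VR exposures, the fluctuations of skin conductance (SC) were measured for all patients". Data collection procedure also refers to SC fluctuations, and sets the reference period: "the signal of SC for each participant was taken before the study procedure start for 5 min".
- **Analysed quantity.** Main analyses defines the individual score thus: "a difference score in the area under the curve between the last 5 min of measurement and baseline level of SC will be extracted". A Pearson correlation will then "examine the relationship between the level of SC and pain intensity", with pain taken as the pre-post difference. No count or amplitude of fluctuations is defined, and the AUC is not said to be that of a phasic component.
- **Preprocessing.** The raw signal is inspected visually and then smoothed with a factor of three samples. The smoother is described as "replacing the high-frequency signal with the mean values across three milliseconds to subtract the artifacts, without changing the wave form".
- **Recording conditions.** Under Pain, electrodes go on the non-dominant hand and "patients were instructed not to move for the duration of the recording". In the VR arm, patients explore the scenes with a controller during the recording, and in two named environments "patients can freely explore the scenes in 360 degrees for enhancing the feeling of presence and immersion". Control patients are recorded without VR exposure.

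**The concern.** Three stated elements do not fit together.

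1. The article justifies SC by its fluctuations but scores the area under the trace. A patient's score may then say little about the indicator, or may point the other way.
2. The smoother is given a task that it can perform only for very fast noise. A reader may believe that artefacts have been dealt with when only the inspection step could do so.
3. Patients are told to keep still, but one arm is given a task that involves a controller and looking around.

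At stake is the SC-pain correlation, the only SC analysis that the article describes. No adjustment for arm is mentioned. If the arms are pooled, any shift in SC caused by the VR task, combined with the larger pain reduction hypothesised in that arm, could produce a correlation even if SC does not track pain within either arm. That could be misread as support for the physiological indicator.

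**Working it through.** **1. What the AUC score measures.** Both windows last 5 min = 300 s (Data collection procedure; Main analyses). The area under a trace over a fixed window is its duration times its mean, so

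score = 300 × (mean SC in last 5 min − mean SC at baseline).

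This is a change in level, which agrees with the article's own description of the correlated quantity.

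*Can it move against fluctuations?* The article gives no amplitudes, so these are assumptions: a level of 5 units, and each fluctuation shaped as 0.1 × (e^(−u/4) − e^(−u/0.75)), where u is seconds from onset. Each fluctuation then has area 0.1 × (4 − 0.75) = 0.325 unit·s.

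| Level | Fluctuations | AUC = 300 × level + 0.325 × number | Against first row |
|---|---|---|---|
| 5.0 | 10 | 1500 + 3.25 = 1503.25 | reference |
| 5.0 | 60 | 1500 + 19.5 = 1519.5 | +1.1% |
| 5.5 | 10 | 1650 + 3.25 = 1653.25 | +10.0% |
| 4.5 | 60 | 1350 + 19.5 = 1369.5 | −8.9% |

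Synthetic traces gave the same values to within 0.01. In the last row fluctuations rise sixfold and the AUC falls.

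*Range.* Fifty extra fluctuations add 50 × 0.325 = 16.25 unit·s. A fall in level of more than 16.25/300 = 0.054 units (1.1% of 5) cancels them. If each fluctuation is five times larger, the fall needed is 81.25/300 = 0.27 units (5.4% of 5). The break-even point depends on amplitude. That the score mixes level with fluctuations does not.

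**2. What the smoother removes.** Three samples equal three milliseconds only at 1000 Hz. The sampling rate is not stated, so this is inferred. A three-point mean has gain

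H(f) = (1 + 2 cos(2πf/fs)) / 3.

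With fs = 1000 Hz:

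| Frequency | Amplitude passed |
|---|---|
| 1 Hz | 99.999% |
| 5 Hz | 99.97% |
| 10 Hz | 99.87% |
| 50 Hz | 96.7% |
| 155 Hz | 70.7% (half power) |

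*Range.* For sampling rates from 50 to 2000 Hz, the half-power point runs from about 7.8 to 311 Hz, and attenuation at 1 Hz is never above 0.53%. In a synthetic 5-minute trace with 28 assumed artefacts of 0.5 s and 1 unit, the AUC rose by 28 × 0.5 × 1 = 14, from 1503.2 to 1517.2, and was still 1517.2 after smoothing.

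**3. What pooling the arms could do.** Suppose the within-arm correlation is zero and the arms are equal in size. Let the arms differ by Dp within-arm SDs in pain change and Ds in the SC score. Then

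pooled r = (Ds × Dp / 4) / √[(1 + Ds²/4)(1 + Dp²/4)].

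For Dp, use the two effect sizes in Study sample size (0.49 and 1.08), assumed here to apply to the change score. Ds is unknown; 0.5 and 1 are assumed.

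| Dp | Ds = 0.5 | Ds = 1 |
|---|---|---|
| 0.49 | 0.1225·0.5/√(1.0625 × 1.0600) = 0.06 | 0.1225/√(1.25 × 1.0600) = 0.11 |
| 1.08 | 0.27·0.5/√(1.0625 × 1.2916) = 0.12 | 0.27/√(1.25 × 1.2916) = 0.21 |

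These are sizes only; the sign follows the direction of the SC shift. If the arms do not differ in SC, the distortion is zero.

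**The case against.** **Safeguards exist, and this stands.** Visual inspection comes before smoothing, the electrodes are on the non-dominant hand, there is one controller, patients are told to keep still, and the Discussion says that the analysts will be blinded. The smoother is therefore not the only protection, and a detailed rejection rule may sit in a fuller plan. None of this changes what the article says the smoother itself does.

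**The smoother is said to act on high-frequency signal.** This is fair: for such noise the statement is true. The fault is the unqualified claim that artefacts are thereby removed.

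**Baseline subtraction removes stable differences between patients.** It does. It leaves change in level within the session, which is what the score then measures.

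**A fluctuation count is not immune.** In the synthetic trace the 28 artefacts moved the AUC by only 0.9% (14/1503.2), but could add up to 28 false events to a count. This stands, and is why the remedy needs a rejection rule as well as a new score. A low-pass filter with a cut-off of a few Hz would not help with second-scale artefacts.

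**Stronger readings are not supported.** A reader might infer that VR use is known to produce movement artefacts in these recordings. The article does not say so; it is an inference from the task, and 360-degree exploration is limited to some environments. A reader might also infer a biased between-arm comparison of SC, but Main analyses describes no such test. Nor can a fixed ratio of drift to fluctuation be given: it depends on amplitudes that the article does not state, and other assumed values make fluctuations dominate.

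**Conclusion.** The point holds in limited form. The named indicator and the analysed score are different quantities; this rests on the text and on the identity that area over a fixed window is duration times mean, not on assumed amplitudes. The smoother leaves signal below tens of Hz essentially unchanged at the implied 1000 Hz, and leaves 1 Hz signal essentially unchanged at any sampling rate checked. The no-movement instruction and the VR task need to be reconciled.

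Distortion of the correlation is a possibility, not a demonstrated bias. It requires pooling across arms and an SC shift specific to the VR arm. Under the assumptions shown, a true within-arm correlation of zero could appear as 0.06 to 0.21 in size.

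Although SC is listed under Primary measures, the Outcomes and Main analyses sections make pain intensity the primary outcome, and SC does not enter that model. A reader might infer that the primary result is at risk; it is not. This is a minor to moderate point about a supporting measure.

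**What to change.** 1. From the stored recordings, extract a pre-defined fluctuation measure in the 5-minute baseline and in the last 5 minutes. Use the difference as the SC score and keep the AUC difference as secondary. Alternatively, keep AUC as the main score, rename the indicator as SC level, and drop the claim that it measures fluctuations.
2. Restate the smoother's purpose as reducing high-frequency noise only.
3. Set a written artefact-rejection rule for the visual-inspection step before analysis, apply it masked to arm, and report the share of signal rejected in each arm.
4. Estimate the SC-pain correlation within each arm, or adjusted for arm.
5. Reconcile the no-movement instruction with the VR task, and state that SC recorded during VR may reflect movement or arousal as well as pain.

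The cost is a small amount of analyst time and no new data. Trial status says that data analysis had not been performed when this version was written, so the choice could be fixed before any result was seen.

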**Methods:**

This is a protocol of a parallel RCT conducted in one community hospital. In order to test the efficacy of VR environments for reducing pain intensity, in the following day after surgery, adults (18 to 65 years) will be randomly assigned to either (1) standard treatment after surgery (control group) or (2) VR based intervention along with standard treatment. It is intended that a minimum of 30 patients be recruited in each group. For estimating the intensity of pain, both self-report and physiological measures will be used. Repeated measures of pain outcomes will be taken before and after the intervention. Moreover, for allowing an in-depth investigation of the effect of VR environments, the primary outcome will be complemented with measures of the adverse effects, level of immersion, and level of presence in the VR environment.

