### Outcomes

The present study assesses the efficacy of a Nature Track© VR to decrease pain intensity in surgical patients. The primary outcome is pain intensity measured right before the exposure to the VR content and after. The secondary outcomes measure the effects of the application on relaxation and the amount of time spent by each patient thinking about pain. Also, the primary outcome was complemented with measures of the adverse effects, level of immersion, and level of presence in the VR.

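### Skin conductance is listed as a primary pain measure, but the only analysis stated for it is a correlation with pain change that has no group term: VR is not compared with control, and the correlation is liable to confounding by arm

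*Protocol article*

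**What the plan says.** The abstract's Methods paragraph announces two routes to pain intensity: "For estimating the intensity of pain, both self-report and physiological measures will be used". In the Measures section, under Primary measures, the Pain entry describes the NRS and then adds: "Concomitantly, as a physiological indicator of postoperative pain were measured the fluctuations of the SC". SC is recorded in both arms, with five minutes of baseline and then fifteen minutes with or without VR (sections on the two groups and on data collection).

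The Outcomes section is narrower: "The primary outcome is pain intensity measured right before the exposure to the VR content and after". SC is not named there.

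Main analyses treats the two kinds of data separately. It begins: "Behavioral data will be analyzed using STATA 16.1 in accordance with the intent to treat principal". For the primary outcome: "The effectiveness of the intervention on pain intensity (primary outcome) will be assessed by employing random coefficient analysis", with time, group and their interaction in the model. The same model is extended to a bracketed list of secondary outcomes: "relaxation, time spent by patients thinking about pain, and treatment satisfaction and presence) random coefficient analysis will be performed". Physiological data follow separately. Each patient gets one SC score, the area under the curve in the last five minutes compared with baseline. The only test then named is: "Pearson correlation will be employed to examine the relationship between the level of SC and pain intensity (as a difference score between pre-post intervention").

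**The concern.** Controls are taken to the treatment room and recorded for the same 20 minutes as VR patients, so the data for a between-arm SC comparison are collected by design. The stated analysis does not make that comparison. A correlation between two change scores describes how they move together. It cannot show whether VR changed SC.

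This matters because the Discussion concedes that open-label self-reports may be affected by knowledge of the allocation. SC is the one pain indicator that is not self-reported, and it is left without a treatment estimate.

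The correlation has its own weakness. If assignment to VR moves both SC and pain, patients in the two arms separate on both axes and a correlation appears even when SC and pain are unrelated within each arm. An SC shift unrelated to pain is plausible, since VR patients explore scenes with a controller during recording while controls have no exposure. A reader could then take a significant coefficient as support for SC as a pain marker, or for the NRS result, when it partly reflects assignment.

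**Working it through.** **Step 1. Does any stated analysis compare SC between arms?**

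| Variable | Stated analysis | Group term? |
|---|---|---|
| Pain intensity (primary outcome) | Random coefficient model | Yes |
| Relaxation, time thinking about pain, satisfaction and presence | Random coefficient model | Yes |
| SC | One difference score per patient, then Pearson correlation with pain change | None stated |

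The random coefficient model cannot reasonably be read as covering SC. It is given for named outcomes that exclude SC, the text separates behavioral from physiological data, and SC is reduced to a single score per patient.

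**Step 2. What does a correlation without a group term estimate?** The plan gives no figure to reproduce here. Let d_P be the size of the fall in pain change due to VR and d_S the shift in SC change due to VR (positive if VR raises SC), both in within-arm SD units. Let r_w be the within-arm correlation. With 1:1 arms the variance of the arm indicator is 1/4, so

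r = (r_w − d_P·d_S/4) / √[(1 + d_P²/4)(1 + d_S²/4)].

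Inputs:
- d_P = 0.49 (planning effect) and 1.08 (the other meta-analytic effect), both from Study sample size. Applying them to the pain change score is an assumption.
- d_S is not given. Values up to 1.0 SD in either direction are assumed.
- r_w is not given. Values of 0 and 0.3 are assumed.

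With r_w = 0, in absolute value:
- d_P = 0.49, d_S = 0.5: 0.06125 / √(1.0600 × 1.0625) = **0.058**
- d_P = 0.49, d_S = 1.0: 0.1225 / √(1.0600 × 1.25) = **0.106**
- d_P = 1.08, d_S = 1.0: 0.27 / √(1.2916 × 1.25) = **0.212**
- Either d_P, d_S = 0: **0**

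The sign is positive if VR lowers SC and negative if VR raises it.

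**Step 3. Effect on the test.** Simulation with 30 per arm, 4,000 runs, r_w = 0, nominal two-sided 5%:

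| Pain effect | SC shift 0 | 0.49 SD | 0.8 SD | 1.0 SD |
|---|---|---|---|---|
| 0.49 | 5% | about 7% | about 10% | 12–13% |
| 1.08 | 5% | about 14% | 27–28% | 38–39% |

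**Step 4. If a real within-arm relation exists.** With r_w = 0.3 and d_P = 0.49:
- VR lowers SC by 1 SD: (0.3 + 0.1225)/1.151 = 0.37
- VR raises SC by 1 SD: (0.3 − 0.1225)/1.151 = 0.15

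The same underlying relation can look stronger or weaker depending on what VR does to SC.

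**Step 5. What could a between-arm SC comparison show?** For a two-sample t test on the difference score (two-sided 5%), 30 per arm gives 80% power for d of about 0.74, and 25 per arm for about 0.81. At d = 0.49 power is 46% and 40% respectively.

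**The case against.** Several counter-arguments have force.

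- **Primary status.** A reader might infer that SC is a co-primary endpoint left untested. The documents do not support that. The Outcomes section and Main analyses both name pain intensity as the primary outcome, the Discussion lists it among the self-reported measures, and no section calls SC co-primary. SC is a measure placed under a primary heading. This limits the point but does not supply the missing comparison.
- **An article condenses.** A fuller protocol or SAP might hold an SC comparison. However, this article does not leave SC to another document: it fixes the software, the window, the derived score and the test. The objection weakens the point without removing it.
- **Pooling is inferred.** The article does not say that the correlation is taken over both arms together. That is the plain reading of a Pearson coefficient with no group term or split by arm, but it remains a reading.
- **Confounding is conditional.** A reader might infer that the correlation is confounded outright. It is so only if VR shifts SC as well as pain, and the documents give no SC effect. At the planning effect the spurious r of 0.06 to 0.11 is well below the two-sided 5% threshold of about 0.25 at 60 patients.
- **The remedy is imperfect.** The last five minutes fall during VR, so a between-arm SC difference may reflect arousal or movement as well as pain. This stands and limits how the added estimate may be read.
- **Timing.** SC change is taken during VR and pain change after it. The interval is short, and nothing in the documents makes this more than a minor point.

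**Conclusion.** The point holds in a limited form. As written, the plan lists SC among its primary measures, records it with a baseline in both arms, and gives no VR-versus-control estimate for it. That conclusion rests on the text alone.

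The second part is conditional. The stated correlation is liable to confounding by arm, to a modest degree at the planning effect and materially at the larger cited effect, and not at all if VR leaves SC unchanged. These sizes rest on assumed SC shifts and on reading the correlation as taken across both arms.

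It would go too far to conclude that the efficacy question is half unanswered, or that a between-arm SC result would be a clean, allocation-proof test of pain. The NRS carries the primary question, and SC is recorded under visibly different conditions in the two arms.

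**What to change.** 1. State that the NRS is the primary outcome, consistent with the Outcomes section, and that SC is a supportive secondary measure.
2. Add a between-arm SC estimate: area under the curve in the last five minutes, regressed on group, the five-minute baseline value and type of surgery (randomization was within surgery type), reported with a 95% CI. State in advance that SC is recorded during VR and may reflect arousal or movement, and that 30 per arm gives 80% power only for d of about 0.74 (unadjusted comparison). The interval should therefore carry the interpretation.
3. Replace the unadjusted coefficient with a partial correlation adjusted for arm, or with within-arm correlations shown separately, labelled exploratory.

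The cost is some plan wording and one extra model. No new data are needed, and the Trial status section says that analysis had not been performed, so the change could still be specified beforehand. The downside is a less precise, non-confirmatory SC result.
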